### Ethical issues

All the trial sites have taken ethical clearance from their institutional review board and submitted the same to the sponsor. The trial registration was initiated after receiving the individual ethics approval letters from all the sites and registration was completed on 13.4.23 (CTRI/2023/04/051620). The eligible participants will be invited to participate in the trial, and sufficient time will be given for them to go through trial-related information and make a decision. Those eligible participants who are willing to participate will be recruited for the trial after obtaining written informed consent in their local language. While no ancillary study has been planned in the current trial, we will take an additional consent for obtaining and storing blood samples for future use in an ancillary study.

### Sequence generation and allocation concealment

Once eligibility is confirmed, web-based randomization will be initiated in the presence of the trial staff. The randomization will be done using PHP as the frontend and MySQL as the backend database. Block randomization stratified for the site and BMI (≥ 23–27 kg/m^2^ and > 27 to ≤ 35 kg/m^2^) will be performed. The randomization will be done in a 1:1 ratio to the intervention or the control arm. The trial staff from each site will enter the participant information following which a randomization number will generated and assigned if they fulfil the eligibility criteria. The random number and the allotted arm details will be provided to the trial staff by an authorized person in each site. The allocation will be concealed until the point of randomization. The allotted intervention will be informed to the clinical team as well as the trial staff, and the trial number will be noted.

### Blinding

The nature of the intervention will preclude blinding of the participant and the caregiver. However, the primary and most of the secondary outcomes are objective in nature and are less likely to introduce detection bias. However, performance bias cannot be ruled out.

### Intervention

In the interventional arm, a focused approach to lifestyle interventions involving customized advice on diet and exercise and a follow-up along with medical advice/treatment as per protocol for those seeking fertility treatment will be offered.

For dietary advise, a dietician will assess the usual dietary intake using 24-h dietary recall and food frequency questionnaire (FFQ) at the clinic. The 24-h recall will help to calculate daily macronutrient and micronutrient composition and the quantum of calories consumed per day.

Following a dietary recall, each woman will be given a customized diet plan as per the recent consensus guidelines for the South Asian region [18]. Diet modification will include a reduction in total calories, refined carbohydrates and fats; avoidance of sugar; and inclusion of normal recommended protein and fibre-rich foods. We will monitor the compliance at 3 and 6 months intervals. Compliance will be monitored using a 24-h dietary recall at the fertility clinic.

For the advice on physical activity, a physiotherapist will assess the physical activity using the G-PAQ questionnaire at the fertility/gynaecological clinic. Subjects who are involved in physical labour or who had to walk or cycle for > 30 min/day and were performing exercises regularly will be asked to continue their routine activities. Subjects engaged in sedentary or light physical activity, as assessed in the initial interview will be advised and regularly motivated to walk briskly for at least 30 min each day. These will be customized for each participant based on their physical limitations and current weight. The compliance at 3 and 6 months intervals by using the G-PAQ questionnaire. The follow-up period will be 6 months for each participant.

### Control

Usual care, which is the medical advice/fertility treatment as per unit protocol for those seeking fertility treatment and one time referral to the dietician for dietary advice and exercise by the physiotherapist in the fertility clinic. There will be no planned follow-up for compliance for the lifestyle intervention in the control arm. The control also will receive the fertility treatment after 3 months following randomization if they do not conceive as per unit protocol. The participant will be reviewed after 6 months to measure the anthropometric and reproductive outcomes at the department of reproductive medicine and surgery/gynaecology outpatient clinic. This visit will be combined with any medical treatment-related appointment to avoid multiple visits to the hospital. As mentioned, the participant in the control arm also will receive medical treatment as per unit protocol 3 months post-randomization if she does not conceive.

### Medical treatment 3 months post-randomization for intervention and control arm

These will be as per standard infertility guidelines starting with letrozole. Ovarian induction may be followed with timed intercourse or IUI (combined male factors such as sexual dysfunction) as per the participant’s profile. The treatment will be given for up to 3 cycles depending on the unit policy, while the lifestyle intervention follow-up will continue in the interventional arm over the next 3 months, to be completed for 6 months.

### Dispensing and scheduling of the individualized lifestyle intervention

#### Weeks 0 and 1 (session 1) (for intervention and control arm)

Post-randomization, same day: blood tests (hormonal and metabolic parameters) and anthropometric measurements, including body weight, will be measured. The blood tests will include blood count, serum follicle stimulation hormone (FSH), serum luteinizing hormone (LH), prolactin, thyroid-stimulating hormone (TSH), dehydroepiandrosterone sulphate (DHEAS), 17 hydroxy progesterone, serum testosterone, sex hormone-binding globulin (SHBG), serum insulin, oral glucose tolerance test with 75 g glucose at 0 and 2 h, fasting lipid profile, HbA1c, uric acid and serum adiponectin. The hormonal and other metabolic parameters will be collected at individual sites and sent to a designated central laboratory for analysis. This central accredited laboratory facility will ensure standardization.

A transvaginal ultrasound will be performed and antral follicle counts and ovarian volume (using TVS with a 6.5 to 8.0 MHz probe). The trial staff will then take the anthropometric measurements while the clinician will obtain the ultrasound report. The clinician will also record information on menstrual regularity and pregnancy status. A pregnancy test will be performed if clinically indicated. The trial staff or nurse will record the quality-of-life score using the prespecified tool [22].

In-person introduction of the programme and the need for weight loss. Participants will be given the food and activity questionnaire and reviewed the same day/week over the phone/in person (flexible). Based on the questionnaire, the dietician and physiotherapist will advise individualized diet/exercise for the intervention arm. For the control arm, one-time advise on diet and exercise will be given (Fig. 1).

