### Inclusion and exclusion

Women attending the fertility clinic will be screened for eligibility. The inclusion criteria will be (i) women aged between 19 and 37 years who have been diagnosed as PCOS by the Rotterdam criteria and wishing to conceive, (ii) body mass index (BMI) ≥ 23 kg/m^2^ but ≤ 35 kg/m^2^ and (iii) duration of infertility ≤ 3 years. The exclusion criteria will be as follows: (i) women planning to take medical treatment at hometown and not available for follow-up period (6 months); (ii) does not have a mobile phone in the house; (iii) pregnancy; (iv) late-onset congenital adrenal hyperplasia (CAH) and androgen secreting tumours; (v) diabetes mellitus, uncontrolled hypothyroidism (TSH > 10 IU/ml), hyperprolactinemia (> 70 ng/ml), bronchial asthma, chronic kidney and liver disease; (vi) prediabetic on metformin or insulin sensitizers or other anti-diabetic medicines; (vii) inflammatory arthritis or any lower limb pathology which precludes exercise; (viii) gastro-intestinal conditions (e.g. ulcerative colitis, Crohn’s disease, coeliac disease) which require special dietary advise; (ix) on anti-psychiatric medications; (x) undiagnosed uterine bleeding; (xi) medical conditions which are contraindications for pregnancy; (xii) previous history of receiving > 6 ovulation induction cycles with letrozole or laparoscopic ovarian drilling; (xiii) previous history of bariatric surgery or planning other strategies for weight loss beyond the trial intervention including but not limited to Fad diets, intra gastric procedures or on weight loss medication; and (xiv) other known causes of infertility which are indications for assisted reproductive technology (ART) treatment, namely severe endometriosis, severe male factor infertility, male partner with azoospermia and documented severe tubal pathology.

Newly detected prediabetics will be included only if they are willing for an initial trial of lifestyle intervention for glycaemic control. We will repeat glycosylated haemoglobin (HbA1c) at 3 months interval, post-randomization, to assess the glycaemic control. If the Hb1Ac is ≥ 6.5%, then initiation of metformin will be considered, and the participant will be followed up as per protocol but will not be considered for per protocol analysis.

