#### Week 26– (session 3) (for both the intervention and control arms)

In person check anthropometry and blood tests (hormones and metabolic parameters) and TVS. The following blood tests will be repeated at 6 months: AMH, serum testosterone, SHBG, serum insulin (fasting and 2 h post-meal), blood sugar (fasting and 2 h post-prandial), fasting lipid profile, glycosylated haemoglobin (HbA1C), SGPT, uric acid and serum adiponectin.

Compliance with dietary intake and physical exercise will be assessed for participants in the intervention and control arms using 24 h diet recall and GPAQ tool.

Medical treatment for infertility can be commenced after 12 weeks on post-randomization in case the participant does not conceive. The lifestyle intervention shall stop at 6 months when a final follow-up on anthropometry, metabolic, hormonal and ultrasound will be done in women from both arms. For those who conceive within 6 months post-randomization, the follow-up will extend until delivery/end of pregnancy for recording obstetrics and neonatal outcomes.

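### Baseline quality of life and anthropometry are recorded after open-label allocation, and four laboratory items have no like-for-like baseline for the 6-month change outcome

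*Protocol article*

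**What the plan says.** All references are to the Protocol article.

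- **Timing.** *Weeks 0 and 1 (session 1)* applies to both arms and opens with: "Post-randomization, same day: blood tests (hormonal and metabolic parameters) and anthropometric measurements, including body weight, will be measured". The ultrasound, the menstrual history and the quality-of-life score follow in the same session: "The trial staff or nurse will record the quality-of-life score using the prespecified tool".
- **Who knows the arm.** *Sequence generation and allocation concealment*: "The allotted intervention will be informed to the clinical team as well as the trial staff, and the trial number will be noted". On masking of the woman and those who treat her, the section *Blinding* adds: "The nature of the intervention will preclude blinding of the participant and the caregiver".
- **Order of eligibility.** The allocation section states: "Once eligibility is confirmed, web-based randomization will be initiated in the presence of the trial staff". It also stratifies randomisation by BMI.
- **Baseline glucose test.** Session 1 lists an "oral glucose tolerance test with 75 g glucose at 0 and 2 h". Serum insulin is listed with no fasting state or time point. AMH and SGPT are not in the list.
- **6-month panel.** *Week 26 (session 3)*: "The following blood tests will be repeated at 6 months: AMH, serum testosterone, SHBG, serum insulin (fasting and 2 h post-meal"). The list goes on with fasting and 2-hour post-prandial glucose, and it includes SGPT.
- **Outcomes.** In *Secondary outcomes*, item (viii) defines weight loss as the difference between baseline and 6 months. Item (xi) is improvement in hormonal and metabolic parameters relative to baseline, glycaemic parameters included. Item (x), anthropometry, is a difference at the end of the trial period. Item (xii), quality of life, is an assessment at 6 months.

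**The concern.** A baseline should be fixed before anyone involved in measuring it knows the arm. Here the people who weigh and measure the woman know her allocation, and she may know it too when she answers the questionnaire. A woman told she will have individualised advice with follow-up, or a single advice session, may rate her quality of life differently that day. Such a shift would not be a treatment effect. It would enter any change score in full and any baseline-adjusted comparison in part.

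The second problem is independent of the first. Outcome (xi) compares each woman with her own baseline, but some tests called repeats at 6 months either are not in the baseline list or are done under different conditions. A 2-hour glucose after a standard load and one after a meal do not measure the same thing, so their difference mixes a change in the woman with a change in the test.

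Some of the post-randomisation tests also bear on eligibility, although eligibility is said to be settled before randomisation.

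**Working it through.** **1. Scale of the trial.** No figure in the plan is in dispute on this point. The sample size reproduces: (1.960 + 1.282)² × (0.30×0.70 + 0.40×0.60) / 0.10² = 472.8, so 473 per arm. For attrition, 946 / 0.80 = 1182.5, so 1183, rounded in the plan to 1200. It rests on live birth and uses no baseline measurement. For the secondary outcomes I take 600 per arm, or 600 × 0.80 = 480 after the plan's 20% attrition.

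**2. What an arm-aware baseline could do.** The article gives neither an SD nor a correlation for quality of life or weight, so this is an illustration. Assume no true effect, equal SDs at both visits, baseline-to-6-month correlation ρ of 0.3 to 0.7, and a baseline shift of d SD in one arm only. In SD units:

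- Change score: bias d, SE = √[2(1−ρ) × 2/n].
- Baseline-adjusted: bias ρd, SE = √[(1−ρ²) × 2/n].
- False-positive rate = 1 − Φ(1.96 − bias/SE) + Φ(−1.96 − bias/SE).

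Worked case, n = 480, ρ = 0.5, d = 0.10:

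- Change score: SE = √(2 × 0.5 × 2/480) = 0.0645, bias/SE = 1.55, rate 34%.
- Adjusted: bias 0.05, SE = √(0.75 × 2/480) = 0.0559, bias/SE = 0.89, rate 14.5%.

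Ends of the range:

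| Assumed shift | n, ρ | Change score | Baseline-adjusted |
|---|---|---|---|
| 0 | any | 5% | 5% |
| 0.05 SD | 480, 0.3 | 10.0% | 5.7% |
| 0.05 SD | 600, 0.7 | 20.1% | 13.6% |
| 0.10 SD | 480, 0.3 | 25.8% | 7.8% |
| 0.10 SD | 600, 0.7 | 60.9% | 39.7% |

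An unadjusted comparison of 6-month values does not use the baseline and stays at 5%.

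**3. The two test lists side by side.**

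| Item | Session 1 | Week 26 |
|---|---|---|
| Testosterone, SHBG, fasting lipids, HbA1c, uric acid, adiponectin | listed | listed |
| Fasting glucose | listed (0 h of the glucose test) | listed |
| Insulin | listed, time point not stated | fasting and 2 h after a meal |
| 2-hour glucose | after 75 g glucose | post-prandial |
| AMH | not listed | listed as a repeat |
| SGPT | not listed | listed as a repeat |

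Four items lack a like-for-like baseline: 2-hour glucose, 2-hour insulin (as far as stated), AMH and SGPT. VAI and LAP rest on lipids and anthropometry, both taken at both visits, so they have a matching baseline.

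**4. Eligibility tests.** *Inclusion and exclusion* rules out diabetes, raised TSH, raised prolactin and late-onset CAH, with diabetes defined by fasting glucose, 2-hour glucose or HbA1c. It adds: "Newly detected prediabetics will be included only if they are willing for an initial trial of lifestyle intervention for glycaemic control". TSH, prolactin, 17-hydroxyprogesterone, the glucose test and HbA1c all appear in the post-randomisation panel. The article does not say whether earlier results exist.

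**The case against.** Much of the opposing case stands.

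- **Analysis.** Quality of life is defined as a 6-month assessment, not as change, and the main analysis of continuous endpoints is a z-test on means. If 6-month values are compared directly, an arm-aware baseline does no harm. The article also does not say whether the woman learns her arm before the questionnaire. The concern about quality of life is therefore conditional.
- **Weight.** A weight must already exist before randomisation, because BMI is an entry criterion and a stratification factor. The measurement is objective and is described before the advice is given. The risk is small, but outcome (viii) is a change score and the article does not say which weight serves as baseline.
- **Bloods.** Knowledge of the arm can hardly alter samples drawn the same day and assayed centrally.
- **Panel.** AMH and SGPT are not named in outcome (xi). Calling them repeats suggests that they were simply left out of the session 1 list. That explanation does not cover the change of 2-hour test.

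Two stronger readings are tempting. One is that eligibility is decided after allocation, so that women are removed and the intention-to-treat set is damaged. The documents do not support this. Eligibility is confirmed before randomisation, prediabetic women's willingness is a condition of inclusion, and *Statistical analysis* keeps all randomised women in the intention-to-treat set. Separate screening tests are possible, and the schedule in Fig. 1 is not reproduced in the text at hand. What remains is an ambiguity to clear up. The other reading is that the whole comparison with baseline is compromised. It is not: lipids, HbA1c, fasting glucose, testosterone, SHBG, VAI and LAP have matching measurements.

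**Conclusion.** The point holds in limited form, for secondary outcomes only.

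- **Timing.** Followed as written, the plan yields baseline quality of life and anthropometry recorded by staff who know the arm. This matters mainly for quality of life, if it is analysed as change or adjusted for baseline, and to a lesser degree for weight loss. Its size cannot be derived from the documents. The calculation shows only that, at this sample size, even a 0.05 SD shift would be enough to matter; it does not show that a shift will occur.
- **Panels.** Change from baseline is not like for like for 2-hour glucose, 2-hour insulin, AMH and SGPT. This follows from the text, except that insulin rests on an unstated baseline time point and AMH and SGPT may be a listing omission.
- **Eligibility.** The sections on inclusion, allocation and session 1 leave unclear which results confirm eligibility.

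Live birth, its intention-to-treat analysis and the sample size are unaffected. The changes are worth making because they are cheap and remove an avoidable bias and a non-comparable measure.

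**What to change.** 1. Record quality of life and anthropometry before the web randomisation, and name those values as the baseline for outcomes (viii) and (xii). A weight is already needed at that point for BMI stratification.
2. Use the same 2-hour test for glucose and insulin at both visits and state the insulin time points. Otherwise limit the glycaemic change outcome to fasting values and HbA1c.
3. Add AMH and SGPT to the session 1 draw, or report them only as between-arm comparisons at 6 months.
4. Reconcile *Inclusion and exclusion*, *Sequence generation and allocation concealment* and *Weeks 0 and 1 (session 1)* by stating which results confirm eligibility before randomisation.

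**Cost.** One visit is reordered and at most two assays are added to an existing draw, or none if those outcomes are restricted. Item 4 needs only a clarifying sentence if screening results already precede randomisation. For women already randomised under the present order, quality of life can be compared on unadjusted 6-month values, which an arm-aware baseline does not affect.

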### Secondary outcomes

There will be several secondary outcomes which will measure clinical, endocrinological and quality of life parameters and are listed below:(i)Clinical pregnancy rate (time frame: 0 to 9 months post-randomization for participants who conceive within 6 months following randomization): ultrasound evidence of gestational sac or definitive clinical evidence of pregnancy. An ectopic pregnancy will also be considered a clinical pregnancy [24].(ii)Ongoing pregnancy rate (time frame: 0 to 9 months post-randomization for participants who conceive within 6 months following randomization): a viable intrauterine pregnancy as documented by ultrasound after 12 completed weeks of gestation.(iii)Miscarriage rate (time frame: 0 to 12 months post-randomization for participants who conceive within 6 months following randomization): miscarriage is defined as a spontaneous loss of pregnancy before 20 completed weeks of gestational age [23].(iv)Ectopic pregnancy rate (time frame: 0 to 9 months post-randomization for participants who conceive within 6 months following randomization): ectopic pregnancy is defined as pregnancy outside the uterus as diagnosed by ultrasound, surgically or by histopathology [24].(v)Stillbirth: defined as the death of a foetus prior to the complete expulsion or extraction from its mother after 20 completed weeks of gestational age [23].(vi)Time to pregnancy (time frame: 0 to 8 months post-randomization for participants who conceive within 6 months following randomization): from randomization to the documentation of pregnancy (calculated in days).(vii)Positive pregnancy rate (time frame: 0 to 7 months for participants who conceive within 6 months following randomization): defined as positive urine pregnancy test or serum beta human chorionic gonadotrophin (hCG) > 5 IU/ml.(viii)Mean weight loss (time frame: 6 months post-randomization): difference between baseline and follow-up at 6 months).(ix)Improvement in menstrual regularity (time frame: 6 months post-randomization): (according to the International Federation of Gynecology and Obstetrics (FIGO) 2018 guidelines variation of the cycle to be called regular is 7–9 days depending on age. Age 18–25 years ≤ 9 days; age 26–41 years ≤ 7 days is regular); proportion of women in whom regularization of the menstrual cycle is recorded by a total number of women in whom menstrual regularity is recorded.(x)Differences in anthropometric parameters (time frame: 6 months post-randomization) (waist circumference, hip circumference, neck circumference, waist hip ratio, waist height ratio and wrist circumference) at the end of the trial period.(xi)Improvement in hormonal and metabolic parameters (time frame: 6 months post-randomization) [biochemical markers such as lipid profile and glycaemic parameters, visceral adiposity index (VAI) and lipid accumulation product (LAP)] over the baseline.(xii)Quality of life (PCOS specific) assessment (time frame: 6 months post-randomization) [22].(xiii)Pregnancy-related complications (time frame: 0–17 months post-randomization for participants who conceive within 6 months following randomization) (GDM, PIH, preterm birth): obstetric outcomes—gestational diabetes, hypertensive disorder of pregnancy, preterm delivery (< 37 weeks), very preterm birth (< 32 weeks), low birth weight (< 2500 g) or high birth weight (> 4000 g)

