### Statical analysis

Data will be entered using ICMR software (developed by ICMR, New Delhi) and screened for outliers and extreme values using Box-Cox plot and histogram (for the shape of the distribution). Summary statistics will be used for reporting demographic and clinical characteristics using mean (SD)/median (range) for the continuous variables, and frequency along with percentage for categorical variables. An intention-to-treat analysis and per-protocol analysis for the primary and secondary endpoints will be performed. The continuous endpoints will be tested using *z*-test for means, and the difference in means will be presented with 95% CI. The categorical endpoints will be tested using *z*-test for proportions and the difference in proportion will be presented with 95% CI. A generalized estimating equations (GEE) will be performed to understand the compliance and the effect over time between the two groups of intervention. To understand the advantage of intervention the number needed to treat will be presented.

Based on BMI 23–27 and > 27–35 kg/m^2^, we will perform subgroup analysis to explore whether there is any difference in the effect of the intervention in different subpopulations.

All the randomized subjects will be included in the intention to-treat (ITT) analysis. The ITT analysis is done for the primary endpoint and secondary endpoints and analysed according to the group assigned by randomization. For dropouts with no information on the outcome, it will be assumed that the intervention did not result in a live birth (Table 1).

Per-protocol set (PPS) is the subset of ITT, where the subjects are randomized and treated without any major protocol deviations that impacts the efficacy of the results. The PSS will be used for primary endpoint analysis and secondary end-points. The analysis set will be the subset of participants who are not dropped out of the study and satisfy the protocol requirement. Non-compliant will not be considered for the per-protocol analysis but will be included in the ITT (Table 1). We will perform additional analysis for partially compliant participants and include them in the per-protocol analysis (Table 1). The analysis will be performed by creating an interaction term for the intervention group with partially and fully complaint groups presenting multiple testing-adjusted *p*-values.

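### The PCOS quality-of-life score is recorded after randomization by staff who know the arm, its mode of administration is not stated, and the plan's argument on detection bias does not cover it

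*Protocol article*

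**What the plan says.** All references are to the protocol article.

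- **Who records the score.** The section on weeks 0 and 1 (session 1, both arms) says "The trial staff or nurse will record the quality-of-life score using the prespecified tool".
- **When.** The same section places the session after allocation: "Post-randomization, same day: blood tests (hormonal and metabolic parameters) and anthropometric measurements, including body weight, will be measured".
- **What the recorders know.** Under sequence generation and allocation concealment: "The allotted intervention will be informed to the clinical team as well as the trial staff". A nurse belongs, on any natural reading, to one of those two groups.
- **Blinding.** "The nature of the intervention will preclude blinding of the participant and the caregiver". The section then argues that "the primary and most of the secondary outcomes are objective in nature and are less likely to introduce detection bias", and concedes that performance bias cannot be excluded.
- **The outcome.** PCOS-specific quality of life is secondary outcome (xii), assessed at 6 months.
- **The 6-month visit.** The week 26 section begins "In person check anthropometry and blood tests (hormones and metabolic parameters) and TVS" and goes on to diet and exercise compliance. It does not mention the quality-of-life score or who takes it. The schedule of assessments is a figure that is not reproduced in the text available here.
- **Analysis.** Continuous endpoints are compared by a z-test for means, and "the difference in means will be presented with 95% CI".

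**The concern.** Quality of life is a subjective score. The article names the people who record it and says they are told the arm. Its only argument against detection bias is objectivity, which does not apply to this outcome, and it states no other safeguard for it.

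By 6 months the arms also differ in contact with the team. The intervention arm has had weekly messages, monthly telephone calls and an extra visit at week 13. If the same staff put the items to the women, knowledge of the arm could affect how questions are asked or answers are taken down.

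At stake is the credibility of a quality-of-life benefit. The trial is sized for live birth, so it is large for a continuous score. Sample size reduces random error but not a systematic shift, and a modest shift can therefore reach significance. The Discussion lists quality of life among the domains important to these women, so a positive result is likely to be reported.

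**Working it through.** **1. The plan's own figure.** Inputs from the sample size section: 30% live birth under usual care, 10 points' improvement (40%), alpha 0.05, power 90%. Sidedness is not stated; two-sided is assumed because it reproduces the figure.

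n per arm = (1.960 + 1.282)² × (0.3×0.7 + 0.4×0.6) / 0.10² = 472.8, so 473 per arm and 946 in total. With 20% attrition, 946 / 0.80 = 1182.5, so 1183, which the plan rounds to 1200 (600 per arm). The figure is reproduced. It concerns live birth only; the article gives no SD, target difference or power for quality of life.

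**2. Women with a 6-month score.** 600 × (1 − 0.20) = 480 per arm if the planned attrition applies to this outcome.

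**3. Smallest significant difference.** In units of the SD of the score compared, SE = √(2/480) = 0.0645. Two-sided significance at 0.05 needs an observed difference of 1.96 × 0.0645 = 0.127 SD.

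**4. Effect of a pure recording shift.** Let the true difference be zero and the between-arm shift be b SD. The chance of p < 0.05 is

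Φ(b/SE − 1.96) + Φ(−b/SE − 1.96).

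For b = 0.10: b/SE = 1.549, giving Φ(−0.411) + Φ(−3.509) = 0.34. For b = 0.20: b/SE = 3.098, giving Φ(1.138) = 0.87, the second term being negligible.

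The size of b is an assumption, so a range is shown. The 360-per-arm column assumes 40% missing scores; the 600-per-arm column assumes none.

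| Shift (SD) | 360 per arm | 480 per arm | 600 per arm |
|---|---|---|---|
| 0 | 5% | 5% | 5% |
| 0.05 | 10% | 12% | 14% |
| 0.10 | 27% | 34% | 41% |
| 0.15 | 52% | 64% | 74% |
| 0.20 | 77% | 87% | 93% |
| 0.30 | 98% | 99.6% | 99.9% |
| Significance threshold | 0.146 SD | 0.127 SD | 0.113 SD |

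**5. Is the tool administered by staff?** The session 1 text uses two wordings. Participants are given the food and activity questionnaire, whereas the quality-of-life score is something staff record, the same verb as for the clinician noting menstrual regularity. The contrast makes staff administration the natural reading, but it does not establish it.

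**6. Does the procedure carry over to 6 months?** The sentence on recording belongs to session 1 alone. The week 26 text gives no other procedure, so carrying it forward is a reasonable inference and no more than that.

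**The case against.** The strongest reply is that the article never says the women are interviewed. Recording a score is compatible with taking down a form that the woman filled in. The mode may be fixed by the cited tool, or by a fuller protocol that is not shown, and a condensed article need not spell it out. This stands against any claim that the plan prescribes interviews. It does not remove the point: the article itself names arm-aware recorders and offers a bias argument that does not reach this outcome. If self-completion is already intended, one sentence settles it.

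Second, the Blinding section does not dismiss detection bias. It speaks of most secondary outcomes and of a lower likelihood, and it admits performance bias. That is correct, and nothing there is false. The exception is simply left unnamed.

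Third, the woman is the source of the answers and knows her own arm, so self-completion leaves her own reporting bias untouched. This also stands. No figure in the documents separates the recorder's share from hers.

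Fourth, the size of the shift is hypothetical, and the same arithmetic would apply to any subjective outcome in a trial this large. That is true. The table shows how little protection the sample size gives; it does not show that a shift will occur.

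Finally, this is one of thirteen listed secondary outcomes, and the main conclusion does not depend on it. That limits the weight of the point.

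**Conclusion.** The point holds as a cheap improvement. A subjective outcome is recorded after randomization by staff who are told the arm, and the plan's reliance on objective outcomes does not cover it.

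If those staff administer the tool, a differential shift could create a spurious difference. With 480 per arm, a shift of 0.10 SD would be called significant in about 34% of trials and one of 0.20 SD in about 87%, against the nominal 5%. This rests on three assumptions: that staff administer the tool, that the session 1 procedure also applies at 6 months, and that a shift of this size occurs.

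A reader might go further and infer that the large sample will turn recorder influence into a significant benefit. The documents do not support that. They give neither the mode of administration nor a size of bias, and at 0.10 SD most trials of this size would not reach significance. Nor does it follow that self-completion makes the outcome free of bias, since the women are unblinded. The primary outcome and the sample size are unaffected.

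**What to change.** - **Session 1 and week 26 sections:** state that each woman completes the quality-of-life tool herself, in her local language. At baseline she does so before the allocation is disclosed. At 6 months she does so before the compliance assessment and any counselling. A rule that she complete it before meeting any trial staff would not work at baseline, because randomization takes place in their presence.
- **Where reading help is needed:** items are read out verbatim, and the assistance is recorded.
- **Blinding section:** name quality of life as an unblinded, subjective outcome. Say that self-completion removes the recorder's influence only, and that bias from women knowing their arm remains.

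The cost is protocol wording, local-language forms, and moving the baseline questionnaire ahead of disclosure. No separate assessor is needed, although the documents do not say whether local-language versions of the tool exist or how many women would need help. The downside is some unanswered items and assisted completion for women who cannot read. The intervention, the visits and the 1200 sample stay as they are.
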